### Sample size estimation

Our sample size calculation for a community RCT was defined at two levels, i.e. the level of randomisation – number of clusters randomised, and the level of data collection – number of individuals surveyed in each household. Using the method of Hayes and Bennet [12], we estimated sample size (i.e. the number of clusters required in each arm of treatment) for an unmatched cluster-randomised control trial. The calculation made the following assumptions. The proportion in the population that experience any form of IPV (emotional, physical, sexual violence, or all three forms). This estimate is based on national-level data from the 2008 GDHS which indicates that among ever-married women age 15–49 years, 34.9% have experienced violence (any form) committed by their husband/partner in the 12 months preceding the GDHS survey [8]. We powered the study to detect a 30% reduction in violence in the intervention arms and took alpha (ɑ) = 0.05 (two-sided), set power at 90% and estimated the coefficient of variation (k) between clusters (localities) for the outcome measure to be k = 0.20 based on district-level census data from the Central Region of Ghana [11]. We planned to oversample by 15% to allow for incomplete questionnaires. Based on these calculations, a minimum sample size of 820 women and 820 men from 40 clusters per trial arm were sampled at baseline and the same numbers will be sampled again in the post-intervention survey. This would imply 90% power to detect a significant change at the 5% level with a 20% reduction in IPV incidence.

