## Background

Violence against women (VAW) is a global public health burden that has significant consequences for women’s mental and physical well-being, including their reproductive and sexual health [1–5]. Intimate partner violence (IPV), which describes physical, or emotional, or sexual assault, or both, of a spouse or sexual partner, is a common form of VAW in many parts of the world [6], including Ghana [4,5,7–9]. A national study in 1998 revealed that 33% of Ghanaian women experienced physical violence at the hands of their current or previous partners, 29% had their first experience of sexual intercourse by force, whilst 33% of the women had been touched inappropriately against their will [7]. Findings from the Ghana Demographic Health Survey (GDHS) further indicate that among women aged 15–49 years, 36.6% reported experience of physical violence since age 15, 17.2% reported experience of violence in the 12 months preceding the survey and 18.8% reported lifetime experience of sexual violence [8]. Among ever-married women, the GDHS data showed that 34.9% have experienced some form of violence (physical, sexual, or emotional) by a husband or partner in the 12 months preceding the survey [8].

Estimates of IPV prevalence in Ghana have been steadily increasing over the years. In 2011, the UN Women’s violence against women prevalence survey in Ghana reported that between 13% and 61% of ever partnered women in Ghana have experienced a spectrum of lifetime physical violence [9]. While the main perpetrators of physical and sexual violence against women tend to be current or previous husbands and partners; strangers, teachers, schoolboys, other family members and acquaintances may also be perpetrators of physical and sexual violence [4,8]. Violence against women in Ghana is influenced by several factors, including social, economic and legal elements [3,5]. Existing data from the Ghana AIDS Commission (GAC) suggest that Ghanaian women often experience relative powerlessness, compared with men, because of poor economic empowerment and negative social norms [10]. As a result, they are often subject to the will of their partners and husbands. This powerlessness, along with limited life choices, makes it difficult to decline sexual advances without facing coercion or violence [10].

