#### Study outcomes

The main study outcome is past year incidence of IPV (i.e. perpetration of physical and/or sexual IPV for men and experiences for women) which is assessed with the quantitative survey. The questions and response scale used to asses past 12 months IPV experience or perpetration in our population are listed in Table 1. Secondary outcome indicators in our survey address gender attitudes (women’s subordination, Tolerance of VAW, VAW perpetration, and controlling behaviours), social stigma for the victims of VAW, institutional response to VAW, relevant laws on VAW, women and societal responses to VAW and mental health issues). We report of no changes to the trial outcomes after the trial commenced.

**Table 1. T0001:** Tools for measuring past year IPV experience or perpetration among adult women and men in 4 districts of the central region of Ghana.

*Response scale – If yes, how often did this happen? Never Once, More than once*	
IPV EXPERIENCE BY WOMEN	IPV PERPETRATION BY MEN
**Physical violence by intimate partner**	**Physical violence against intimate partner**
● Was slapped or had something thrown at her that could hurt her	**●** Slapped or thrown something at her that could hurt her
● Was pushed or shoved	**●** Pushed or shoved her
● Was hit with fist or something else that could hurt.	**●** Hit her with fist or something else that could hurt.
● Was kicked, dragged, beaten, choked or burnt	**●** Kicked, dragged beat, choked or burnt her
● Perpetrator threatened to use or actually used a weapons against her	**●** Threatened to use or actually used a weapons against her
**Sexual violence by an intimate partner**	**Sexual violence against an intimate partner**
● Was physically forced to have sex when she did not want	**●** Physically forced to have sex when she did not want
● Had sex when she did not want to because she was afraid of what the partner might do	**●** Had sex when she did not want to because she was afraid of what I might do
● Was forced to do something sexual that she found degrading or humiliating	**●** Forced her to do something sexual that she found degrading or humiliating
● Was forced to watch pornography	**●** Forced her to watch pornography
**Emotional abuse by an intimate partner**	**Emotional abuse against an intimate partner**
● Was insulted or made to feel bad about yourself	**●** Insulted or made her to feel bad about herself

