## Data analysis

The main trial analysis will be done by intention to treat. Thus, for intervention districts, data for all respondents will be included whether they report contact with the intervention or not. Any participant who responds affirmatively to any one of the five questions on physical IPV or three questions on sexual IPV in the past 12 months at end line data collection point will be deemed to be an incident case of IPV victimisation (if woman) or perpetration (if man). IPV incidence will be compared between the study arms. Generalised Linear Mixed model for binary outcome (logistic regression) will be used to compare women’s past year experience or men’s perpetration of IPV between the two arms at end-point, adjusting for baseline prevalence. All qualitative data will be coded, and thematic approach will be used to evaluate the impact of the interventions implemented within the communities.

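### The planning rate of 34.9% is for any IPV in ever-married women, but the primary outcome is physical and/or sexual IPV only, so the stated 90% power belongs to a different outcome

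*Protocol article*

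**What the plan says.** The Sample size estimation section of the Protocol article takes as its planning quantity "The proportion in the population that experience any form of IPV (emotional, physical, sexual violence, or all three forms"). The value comes from the 2008 national survey, where "among ever-married women age 15–49 years", "34.9% have experienced violence (any form) committed by their husband/partner in the 12 months preceding the GDHS survey". The Background describes the same figure in the same way: "34.9% have experienced some form of violence (physical, sexual, or emotional) by a husband or partner".

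The outcome is narrower. Study outcomes gives the main outcome as past-year IPV, meaning "perpetration of physical and/or sexual IPV for men and experiences for women". Data analysis fixes the case definition for both sexes: a respondent is a case on a positive answer to "any one of the five questions on physical IPV or three questions on sexual IPV in the past 12 months". Table 1 lists emotional and economic items, but they do not make a case.

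The recruitment section admits women aged 18 to 49 and men aged 18 or over, on residence, language and capacity to consent. It states no marriage or partner requirement. Sample size estimation assigns 820 women and 820 men per arm, yet the only rate it gives is women's experience.

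The same section sets k = 0.20 between localities for the outcome, "based on district-level census data from the Central Region of Ghana". It names a 30% reduction as the target, and ends by claiming 90% power for a 20% reduction.

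**The concern.** A power statement holds for the outcome whose rate went into it. Here the rate includes women whose only past-year experience was emotional abuse, and the analysis will not count them as cases. With a lower control rate, the same relative reduction is a smaller absolute difference, and the sampling noise is larger relative to it. The planned localities then give less power than stated.

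For men the issue is different. Reported perpetration is another measure in another population, and nothing in the article supports 34.9% for it in either direction.

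What is at stake is how a null result is read. If either sex shows no difference, readers would take it as coming from a test with 90% power, when it could easily reflect low power.

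**Working it through.** **Inputs.** Control rate p0 = 0.349, k = 0.20, two-sided alpha 0.05 and reductions r of 30% and 20%, all from Sample size estimation. The layout is 20 localities per arm with about 82 households each (Abstract), with women and men in different localities (Selection and randomisation of study sites). With 820 per sex per arm, that gives 820/82 = 10 localities of m = 82 per sex per arm.

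**Formula.** This is the unmatched method that the article cites, with p1 = p0(1 − r) and c localities per arm:

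c = 1 + (z_α/2 + z_β)² × V/(p0 − p1)², where V = p0(1 − p0)/m + p1(1 − p1)/m + k²(p0² + p1²).

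Solved for power: Φ[(p0 − p1)/√(V/(c − 1)) − 1.96].

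**The plan's own figure.** At p0 = 0.349 and a 20% reduction:

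- 10 localities × 82, one sex: 44%.
- 20 localities × 82, sexes pooled: 75%.
- 40 clusters per arm read literally, sexes pooled, 1640/40 = 41 each: 89%.

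Only the last reading comes near the stated 90%, and it conflicts with 40 localities in total. For a 30% reduction, 10 × 82 gives 81%:

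- p1 = 0.2443 and p0 − p1 = 0.1047.
- V = 0.00277 + 0.00225 + 0.00726 = 0.01228.
- √(0.01228/9) = 0.0369.
- 0.1047/0.0369 = 2.83, and Φ(2.83 − 1.96) = 0.81.

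The gap between 90% and these figures arises at the article's own rate. It comes from the number of localities and from the two different target reductions, not from the mismatch examined here.

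**Direction of the mismatch.** Physical/sexual IPV is a subset of emotional, physical or sexual IPV. Within the surveyed women its rate is therefore at most 34.9%, with equality only if none of them reported emotional abuse alone. Dividing V by p0² gives

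(1 − p0)/(m·p0) + (1 − r)(1 − (1 − r)p0)/(m·p0) + k²(1 + (1 − r)²).

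The first two terms grow as p0 falls and the third does not change. At fixed k and fixed relative reduction, a lower control rate therefore always lowers power.

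**Size of the mismatch.** The article gives no rate for the actual outcome, so the lower rates below are assumptions (10 × 82 per sex per arm, k = 0.20).

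| Control rate | Power, 30% reduction | Power, 20% reduction |
|---|---|---|
| 34.9% (plan) | 81% | 44% |
| 30% | 77% | 41% |
| 25% | 72% | 38% |
| 20% | 66% | 33% |

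Localities per sex per arm for 90% power at a 30% reduction rise from 12.8 at 34.9% to 15.5 at 25% and 17.9 at 20%.

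**Other layouts.** The fall does not depend on one cluster count. From 34.9% to 25%, 20 localities × 41 of one sex per arm (30% reduction) goes from 93% to 85%. Forty clusters × 41, pooled (20% reduction), goes from 89% to 80%.

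**Sensitivity to k.** At 34.9%, 10 × 82 and a 30% reduction, power is 91% for k = 0.15 and 69% for k = 0.25. Both k values are assumed. The input whose source is at district level therefore matters about as much as the rate.

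**The case against.** Several points on the other side have force.

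- **Men.** A reader might infer that the control rate is overstated for both sexes. The document does not show that for men. With no perpetration rate, 34.9% is unsupported, not proven too high.
- **Unpartnered respondents.** A reader might infer that they enter the denominator as non-cases. No partner criterion is stated, but how such respondents are routed through the IPV items is a detail that an article commonly leaves to the full protocol. Never-married women with partners can also be cases. A lower rate from this source is probable, not certain.
- **The 17.2% figure.** The Background reports that "17.2% reported experience of violence in the 12 months preceding the survey" among women aged 15–49, and a reader might take this as the true control rate. It stands in a sentence on physical violence, is not limited to partners and is not the trial outcome. It would give 61% power for a 30% reduction, but it cannot serve as an estimate.
- **Place and time.** The source is national and from 2008, while the trial covers one region in 2016 to 2018. The Background says that prevalence estimates have been rising. This could offset part of the mismatch by an unknown amount.
- **Attribution.** The fall from 90% to 81% comes from the cluster layout. Only the step down from 81% belongs to the rate.
- **Analysis.** Adjusting for baseline prevalence may reduce residual between-locality variation. At k = 0.15, power would be 82% at a 25% rate. In the other direction, the article describes the random draw at district level, so locality-level formulas may flatter the design.
- **Pooling.** Pooling the sexes (20 × 82) keeps 96% at a 25% rate for a 30% reduction. But experience and perpetration are different outcomes, and the stated 20% reduction has only 75% even at 34.9%.

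These points limit how large the effect can be said to be. None removes the conflict between the planned and the tested outcome.

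**Conclusion.** The point holds. The planning rate and the case definition describe different outcomes, and this follows from the article's own text. For women in the surveyed population, the right rate is at most 34.9% and probably lower. For men the rate is unsupported. The value of k for localities rests on district-level data.

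The stated 90% power therefore does not apply to the outcome tested. The mismatch by itself costs about 4, 9 or 15 percentage points of power for a 30% reduction at assumed rates of 30%, 25% or 20%. For a 20% reduction it costs about 3, 7 or 11 points. These figures rest on 10 localities of 82 per sex per arm, k = 0.20, the cited formula and no gain from baseline adjustment. Confidence is high that the outcomes differ, but not in the size of the effect, because the true rate is not in the document.

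**What to change.** Keep the existing calculation on record, and add that it used any IPV (emotional, physical or sexual) in ever-married women.

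Then use the completed baseline survey to estimate two quantities, separately for women and for men, under the actual eligibility and the Data analysis case definition: the past-year physical/sexual IPV rate, and the between-locality k. Restate power, or the detectable reduction, for each sex with the actual number of localities, and say whether respondents without a partner are in the denominator.

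The cost is a few hours of analysis on data already collected and one revised paragraph. No new fieldwork is needed, and the analysis does not change. The downside is that the stated power will probably be lower.

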#### Selection and randomisation of study sites

The selection of intervention and control districts was done using a census map of the Central Region that showed Inland and Coastal districts. After excluding some districts because of previous VAW-related intervention activities conducted by the Gender Studies and Human Rights Documentation Centre (Gender Centre; two inland and two coastal districts were then purposively selected as study sites. Designated sites are separated from each other by a geographical buffer (at least one district wide) to reduce the possibility of intervention diffusing into control districts (Figure 1). To randomise the districts, the names of the two Inland districts were written on a piece of paper and placed in a bag. One paper was blindly drawn from the bag and the selected district was assigned as an intervention district, while the other was designated as the control district. Clusters in the Ghana Demographic and Health Survey (DHS) are census listed localities with each locality comprising one or more Enumeration Areas (EAs). Within each selected district, a list of localities was obtained from the Ghana Statistical Service (GSS). All localities were allocated numbers, placed in a bag and blindly drawn. A total of 40 localities, (10 per district) were selected to serve as clusters. Since localities comprise several EAs, there was a second layer of stratification such that within each district, women and men participants were drawn from different localities(Figures 2a & b).

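### The planning value k = 0.20 for between-locality variation in IPV is unsupported: it is attributed to district-level census data, and power depends strongly on it

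*Protocol article*

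**What the plan says.** The section on sample size estimation uses the Hayes and Bennett method for an unmatched cluster trial. Its inputs are:

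- **Control proportion.** National survey data for ever-married women, of whom "34.9% have experienced violence (any form) committed by their husband/partner in the 12 months preceding the GDHS survey".
- **Effect.** "We powered the study to detect a 30% reduction in violence in the intervention arms"
- **Error rates.** Two-sided 5% alpha and 90% power.
- **Between-cluster variation.** The coefficient of variation between localities is set "for the outcome measure to be k = 0.20 based on district-level census data from the Central Region of Ghana".

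The section ends with the claim "This would imply 90% power to detect a significant change at the 5% level with a 20% reduction in IPV incidence".

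The source cited for k is also cited in the study setting section. There it supports area, population, literacy, language, unemployment and occupation figures, and nothing on violence.

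On the number of clusters, the abstract gives 40 localities in all, 20 per arm, with about 82 households each. The section on selection and randomisation gives 10 localities in each of four districts and adds that "within each district, women and men participants were drawn from different localities". The sample size section instead speaks of 40 clusters per arm, with 820 women and 820 men per arm.

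**The concern.** The sentence that introduces k names one quantity and cites data for another. The formula needs the spread of true past-year IPV proportions across localities. The stated source differs in level (districts, not localities). By every other use the article makes of it, it also differs in subject (census characteristics, not IPV). The absence of a derivation would not count against a condensed article. The point is that the source it does state does not fit the quantity it states.

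This matters because, with about 82 respondents per locality, variation between localities is the larger part of the variance. A modest error in k moves power by ten points or more in the analysis of one sex. If power is overstated, a null result may be read as absence of effect when the trial had little chance of detecting one.

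**Working it through.** **Inputs.** p0 = 0.349 (sample size section). p1 = 0.349 × 0.70 = 0.2443 for a 30% reduction, or 0.349 × 0.80 = 0.2792 for 20%. m = 82 per locality (abstract). c = 20 localities per arm (abstract). For one sex, c = 10 per arm is inferred: 820 ÷ 82 = 10, with women and men in different localities. k = 0.20 is the plan's value; every other k below is an assumption.

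**Formula (unmatched).** Let S = [p0(1−p0) + p1(1−p1)]/m, B = k²(p0² + p1²) and D = (p0−p1)².

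- Clusters per arm: c = 1 + (1.96 + 1.282)² (S + B)/D
- Power: Φ{√[(c−1)D/(S+B)] − 1.96}

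**Step 1: the plan's own 90% for a 20% reduction at k = 0.20.** It is approached only if 40 clusters per arm is taken literally and the sexes are pooled, so that m = 1,640 ÷ 40 = 41.

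- S = (0.2272 + 0.2012)/41 = 0.01045
- B = 0.04 × (0.1218 + 0.0780) = 0.00799
- D = 0.0698² = 0.00487
- √[39 × 0.00487/0.01844] = 3.21, so power is 89.4%

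With the cluster counts given elsewhere in the article, m = 82 and S = 0.00522:

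- 20 per arm: √[19 × 0.00487/0.01321] = 2.65, power 75.4%
- 10 per arm (one sex): √[9 × 0.00487/0.01321] = 1.82, power 44.5%

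These shortfalls arise at the plan's own k. At 10 × 82, even k = 0 does not reach 90% for a 20% reduction.

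**Step 2: weight of k for a 30% reduction, m = 82.** S = (0.2272 + 0.1846)/82 = 0.00502.

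- k = 0.20: B = 0.04 × (0.1218 + 0.0597) = 0.00726, which is 59% of S + B
- k = 0.30: B = 0.09 × 0.1815 = 0.01633, which is 76% of S + B

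**Step 3: power for a 30% reduction as k varies.** D = 0.1047² = 0.01096. At k = 0.20, S + B = 0.01228. Then √[9 × 0.01096/0.01228] = 2.83 gives 80.9%, and √[19 × 0.01096/0.01228] = 4.12 gives 98.5%.

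| k | 10 × 82 (one sex) | 20 × 82 (pooled) |
|---|---|---|
| 0.15 | 90.9% | 99.8% |
| 0.20 | 80.9% | 98.5% |
| 0.25 | 69.0% | 94.6% |
| 0.30 | 57.5% | 87.8% |
| 0.40 | 39.8% | 69.6% |

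Localities per arm needed for 90% power are 12.8 at k = 0.20 and 21.5 at k = 0.30. The largest k that still gives 90% power is 0.155 at 10 × 82 and 0.286 at 20 × 82.

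**Step 4: what the stated source implies about direction.** Variance between localities equals variance between districts plus variance between localities within districts. If 0.20 were the between-district coefficient of variation of IPV, the locality value could not be lower. If 0.20 comes from another census variable, this relation says nothing about whether it is above or below the value for IPV.

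**The case against.** The strongest reply has four parts.

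*The direction is not shown.* A reader might infer that the variance is understated because district data miss the variation within districts. That requires 0.20 to be a district-level figure for IPV, yet the article's other uses of the source suggest it is not. District census data might also list localities, and the source is not available to check. This stands: the value may be too small or too large.

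*The power shortfall has other causes.* The 75.4% and 44.5% for a 20% reduction, and the 80.9% for a 30% reduction in one sex, all occur at k = 0.20. They come from the number of localities and from stating both a 30% and a 20% reduction. With 20 × 82 and a 30% reduction, k can rise to about 0.286 before power drops below 90%. This also stands, but settling those inconsistencies would leave k unsupported, and any restated power needs it.

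*Districts were the units drawn, so a district-level k might be apt.* The sample size section names localities as the clusters. Treating districts as clusters would leave two per arm, with 820 ÷ 2 = 410 of one sex in each. The same formula at k = 0.20 then gives S + B = 0.41182/410 + 0.00726 = 0.00826. So √[1 × 0.01096/0.00826] = 1.15 and power is about 21% for a 30% reduction. This reading does not rescue the claim. It does show that a locality-based figure is optimistic.

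*The inland/coastal layout and baseline adjustment may reduce the relevant k.* That is possible, but the calculation is for an unmatched design and takes no credit for either.

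**Conclusion.** The concern holds in this form: k = 0.20 is defined for one quantity and attributed to data on another, so it is unsupported for locality-level IPV. Power is sensitive to it. For a 30% reduction with 10 localities per arm in one sex, moving k from 0.20 to 0.30 takes power from 81% to 57.5%; with 20 per arm pooled, from 98% to 88%.

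Two stronger readings are not supported. The document does not show that true between-locality variation exceeds 0.20. Nor is k the reason the stated 90% for a 20% reduction fails, since it already fails at k = 0.20 with the 20 localities per arm given in the abstract.

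The figures assume 34.9% in the control arm for both sexes, although that rate covers any form of violence reported by women. They also assume 82 analysable respondents per locality and localities treated as independently allocated. The count of 10 per sex per arm is inferred, and k above 0.20 is illustrative.

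**What to change.** 1. From the completed baseline survey, estimate k between localities for past-year physical and/or sexual IPV, separately for women and men. Remove within-locality sampling variance from the observed spread and give a confidence interval. With about 20 localities per sex (10 per arm × 2 arms), expect a wide interval.
2. Restate power, or the detectable reduction, for the actual number of localities per arm and sex across that interval.
3. State beside the restated figure that districts were the units drawn for allocation, so a locality-based calculation is an upper bound.
4. Keep the census origin of 0.20 on record, since it documents how the trial was planned. Qualify it as a planning assumption not derived from locality-level IPV data, and say how it was obtained.

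The cost is a few hours of analysis of data already collected, with no extra participants. The downside is a power figure that is likely to be less favourable than the one published.

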## Abstract

Violence against women (VAW) is common in Ghana, with nation-wide surveys reporting high prevalence of intimate partner violence (IPV) (physical, sexual and/or emotional violence). Our trial assesses the community level impact of the Rural Response System which uses Community-Based Action Teams ‘COMBAT’ for preventing VAW in Ghana. This study is a mixed method unmatched cluster randomised controlled trial and includes rural (n = 23), peri-urban (n = 7) and urban (n = 10) communities in four districts of the Central Region, Ghana. The trial will last three years with one baseline survey, one impact assessment and a qualitative baseline, midpoint and endline evaluation. A total of 40 localities were selected to serve as clusters (20 per trial arm) with about 82 households per cluster recruited at baseline. The same number will be recruited post-intervention. Adult women (18 to 49 years) and men (≥ 18 years) were drawn from different localities. Sampling of households within a community was random and done using a computerised system. In each selected household, one female or male resident was invited to participate. Individuals are eligible for inclusion in the study if they usually live (sleep and eat) in the household, have lived in the community for at least a year, and are between the ages of 18-to-49 years old. Our impact assessment component will compare past 12 months incidence of IPV (i.e. IPV experiences for women and perpetration of physical and/or sexual IPV for men) between arms in the trial. The implementation of this community trial comes at an opportune time when evidence on the effectiveness of a targeted VAW intervention in the Ghanaian society is needed to inform the development of national policies for preventing VAW. Our progressive research approach using a mixed method design will further extend knowledge globally on a multifaceted intervention to reduce the incidence of intimate partner violence in a developing country.

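### The stated sample does not give 90% power for a 20% reduction in IPV: on the plan's own inputs it gives about 42–45% per sex, and the cluster count per arm is misstated

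*Protocol article*

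**What the plan says.** The Sample size estimation section sets the target: "We powered the study to detect a 30% reduction in violence in the intervention arms", with alpha and power given as "0.05 (two-sided), set power at 90" per cent. The base rate is from national survey data on ever-married women: "34.9% have experienced violence (any form) committed by their husband/partner in the 12 months preceding the GDHS survey". For clustering, the authors "estimated the coefficient of variation (k) between clusters (localities) for the outcome measure to be k = 0.20". They add: "We planned to oversample by 15% to allow for incomplete questionnaires".

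The resulting sample is "a minimum sample size of 820 women and 820 men from 40 clusters per trial arm were sampled at baseline", and the paragraph ends: "This would imply 90% power to detect a significant change at the 5% level with a 20% reduction in IPV incidence".

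The Abstract describes the layout differently: "A total of 40 localities were selected to serve as clusters (20 per trial arm) with about 82 households per cluster recruited at baseline". The section on selection and randomisation of study sites agrees with the Abstract. It gives ten localities in each of four districts, and says that women and men came from different localities within each district. The Data analysis section compares women's experience or men's perpetration between arms at endline.

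**The concern.** One paragraph attaches 90% power to two different effects, 30% and 20%, with no change in base rate, alpha or k. A final sample can exceed a design minimum, so the question is whether the sample taken is large enough to bring the detectable effect down to 20%.

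The same paragraph also gives a number of clusters per arm that is twice the number in the Abstract. In a cluster trial, power depends heavily on that number.

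Readers will use the closing sentence to interpret the endline comparison. If they believe that a 20% reduction would be found nine times in ten, they will take a non-significant result as strong evidence against one. If the true power is below one half, that inference is wrong.

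**Working it through.** **Inputs.** From Sample size estimation: p0 = 0.349; k = 0.20; two-sided alpha 0.05 (z = 1.960); power 90% (z = 1.2816); 820 women and 820 men per arm; 15% oversampling. From the Abstract: 20 localities per arm, about 82 households each.

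**Layout.** 20 localities × 82 households = 1,640 per arm = 820 women + 820 men, so the Abstract's layout accounts for the whole sample. Because women and men come from different localities, 820/82 = 10 localities per sex per arm. Removing the 15% oversample leaves 82/1.15 = 71.3 complete records per locality.

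**Formula** (Hayes–Bennett, unmatched, proportions):

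c = 1 + (1.960 + 1.2816)² × V/(p0 − p1)², where V = [p0(1 − p0) + p1(1 − p1)]/m + k²(p0² + p1²)

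Power = Φ(√[(c − 1)(p0 − p1)²/V] − 1.960)

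**Trying to reproduce the stated 90% for a 20% reduction.** p1 = 0.8 × 0.349 = 0.2792; (p0 − p1)² = 0.0698² = 0.004872. The section's wording, taken literally with the sexes pooled, gives c = 40 and m = 1,640/40 = 41:
- V = (0.2272 + 0.2012)/41 + 0.04 × (0.1218 + 0.0780) = 0.01045 + 0.00799 = 0.01844
- Power = Φ(√[39 × 0.004872/0.01844] − 1.960) = Φ(3.210 − 1.960) = 89.4%, or 86.9% after the 15% allowance

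This comes close to the stated figure, but only with twice the number of clusters per arm given in the Abstract.

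**The layout in the other sections, by sex.** c = 10, m = 82:
- V = 0.4284/82 + 0.00799 = 0.00522 + 0.00799 = 0.01322
- Power = Φ(√[9 × 0.004872/0.01322] − 1.960) = Φ(1.822 − 1.960) = 44.5%
- With m = 71.3, V = 0.01400 and power = Φ(1.770 − 1.960) = 42.5%
- Localities needed per arm and sex for 90% power: 29.5 (m = 82) or 31.2 (m = 71.3), against 10

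**Power for a 20% reduction under other readings:**

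| Reading | Power |
|---|---|
| 20 localities per arm, sexes pooled, m = 82 (71.3) | 75.4% (73.0%) |
| 20 localities per arm, 41 of each sex in every locality | 61.0% |
| 40 clusters per arm, 820 of one sex, m = 20.5 | 72.7% |
| 820 per arm, no clustering at all | 86.2% |

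**What the by-sex layout supports.** For a 30% reduction, p1 = 0.2443 and (p0 − p1)² = 0.01096:
- m = 82: V = 0.01228 and power = 80.9%
- m = 71.3: V = 0.01304 and power = 78.6%
- The smallest reduction with 90% power is 33.9% (m = 82) or 34.8% (m = 71.3)

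**The case against.** **Two effect sizes need not conflict.** The 30% can be read as a design minimum and the 20% as what the final sample achieves. That is fair, and the pair of figures alone proves nothing. The error is that the final sample does not support 20%.

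**The near-90% case uses the stated number of people.** A reader might infer that the 20% claim needs twice the stated sample. It does not: 40 clusters of 41 is 1,640 people per arm, which is exactly 820 women plus 820 men. The conflict is in the number of clusters and in the pooling of the sexes. It suggests, without proving it, that the trial total of 40 was entered as the number per arm.

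**The 42–45% is conditional.** Ten localities per sex per arm is derived, not stated, and the sampling figure is not visible. The separate localities and the by-sex comparison support it. The planned adjustment for baseline prevalence may also lower the between-locality variation. With an assumed residual k of 0.10, power would be 65–69%; with 0.05, 74–79% (10 localities, m = 71.3–82). So the statement that a true 20% reduction is more likely missed than found holds at or near k = 0.20 with separate localities, not in general. But no value of k reaches 90% by sex, since 820 per arm without clustering gives 86%.

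**Low power does not mean that a 20% reduction cannot be excluded.** A reader might draw that conclusion, but exclusion depends on the confidence interval obtained, not on prospective power.

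**The analysis does not use the 20% figure.** True. The correction changes no test and no participant count, only how a null result is read.

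**Conclusion.** The concern holds. The stated 90% power for a 20% reduction is wrong under each reading examined that keeps 20 localities per arm. On the plan's own inputs it is about 42–45% per sex in the layout that the article implies, 61% if both sexes were sampled in every locality, and 73–75% with the sexes pooled. The count of 40 clusters in each arm is a second error in the same paragraph, and the only route found to a figure near 90%.

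In the by-sex layout the 30% target also falls short, at about 79–81%; 90% power holds only for reductions of about 34–35%.

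These figures rest on k = 0.20 without baseline adjustment, on 10 localities per sex per arm, and on two assumptions that probably flatter the design. The base rate is for any form of IPV in women, whereas the main outcome is physical and/or sexual IPV. The formula also treats localities as the randomised unit, whereas the draw described in the site selection section was of districts. Neither is quantified here.

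**What to change.** 1. Delete the closing sentence on a 20% reduction, or restate it with the power that the layout gives.
2. In the same paragraph, correct the cluster count to 40 in total, 20 per arm, in line with the Abstract and the site selection section.
3. State one power figure per sex from the actual layout. On the plan's own inputs this is about 79–81% for a 30% reduction, with 90% power only for about 34–35%. Say that it assumes k = 0.20, the any-form IPV base rate and localities as the randomised unit, and is therefore likely optimistic.
4. Add that a non-significant result should not by itself be read as ruling out a 20% reduction, and that the confidence interval decides this.
5. If the analysis plan, which is not shown, repeats the 20% statement, make the same change there.

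The cost is a few sentences and a less favourable stated figure. No extra participants are needed and the planned analysis does not change.
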